#### Interviews/focus groups

At the conclusion of the RCT, semi-structured focus groups/interviews (*n* = 3, 6–10 in each group, with up to 30 people in total) will be undertaken with groups of the following: (i) clinicians involved in delivery of the service (all service coordinators and up to two other purposively selected clinicians per hospital if they were involved) and (ii) purposively selected participants, based on satisfaction variation from survey results, to further explore the facilitators and barriers to service implementation and delivery. Examples of questions are provided in Table 3.

**Table 3 Tab3:** Example questions and prompts for focus-group interviews^a^

**Service co-ordinators and/or registry staff**	
**Question**	**Prompts**
Can you describe how the service was implemented at your site?	Were any aspects of the protocol provided changed for your site or for a specific clinician, health service or person with stroke?
Can you describe your experience with clinicians/people with stroke/health services/etc.?	Consider was it easy, difficult? Any policies or clinical pathways needing to be changed? Approvals required?
What resources were required to implement? Feedback on resources provided (request copies of changes to documents), including clarity of role and training	Consider information from project team, training, funds, time allocated vs required and other people to be involved?
Were any challenges experienced?	Did any clinician or person with stroke not want to participate? What concerns did they have? If they had concerns, how was this addressed? Were there any shared characteristics for participants withdrawing or refusing participation? Consider how could these be addressed? What resources/factors would be needed?
**Patient participants**	
**Question**	**Prompts**
Can you recall what you thought when you were first contacted by service?	What were your initial thoughts? What sorts of things were discussed?
Can you describe the experience of participating in this service overall?	What sorts of things occurred? Consider referrals, treatments and information
Did you have any concerns or difficulties with the service?	How were these addressed? What resources/factors would be needed?
Were there any benefits to you from participating in the service?	Consider all aspects of health and wellbeing What contributed? If any, do you think they will be maintained?
Anything important to improve the follow-up service?	Consider personnel, integration with existing care, information provided, referrals, accessibility of services and costs associated seeking recommended services or therapies

^a^This is not the full list of questions and prompts

Interviews/focus groups will be conducted remotely (e.g. telephone, video conference), recorded with participant consent and transcribed for analysis.

#### Economic evaluation

A cost consequences analysis will be undertaken to present disaggregated costs and outcomes of implementing the follow-up service [38]. This will clarify which costs and outcomes are most relevant to further refine the design of the service and a future effectiveness trial. Costs of providing the intervention will be estimated based on interviews with clinical leads at participating hospitals and from finance departments, where possible. The impacts of the intervention on resources used by participants will be estimated from a health sector (e.g. hospital presentations, general practitioner visits, specialist visits, outpatient visits) and societal perspective (e.g. employment, household productivity, informal care). Unit prices for resources used and productivity will be obtained from the most contemporary Australian sources. Data from participants will be self-reported, with a diary provided for the duration of the study to assist with collection of data related to health care resources utilised, for example use of health and community services, admissions to hospital or changes to medication (see also Table 1). This information will be supplemented by data from the follow-up service records of all referrals and service contacts for intervention participants. Medical records may also be audited to verify the data collected.

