## Methods

### Research aims

The aim of the study is to assess the feasibility (i.e. acceptability and satisfaction of service coordinators and participants), potential clinical effectiveness, participant resource utilisation and cost implications of the tailored hospital-led follow-up service for chronic stroke compared with usual care (control).

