#### Randomisation, allocation concealment and blinding procedure

Once consented, the trial participants will be randomly allocated 1:1 to the intervention group or control (usual care) group. Online randomisation will occur using REDCap [17], stratified by age (< 65, 65 + years) and sex (male, female) to ensure balance of age and sex between the two groups as these factors are associated with differences in HRQoL [21]. Participants and outcome assessors (AuSCR staff) will be blinded to the group allocation. Service coordinators delivering the intervention will be unaware of participants from their hospital randomised to the control group. To avoid unblinding to group allocation, the control group will not know which group they are in. As part of the study, some participants may be contacted by a member of staff from the hospital or service that treated them for their stroke.

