Clinical evaluation	Quality of life^b^	EQ-5D-3L (baseline: to verify responses from pre-trial is still current, and eligibility is still met for the service)	All participants in conjunction with blinded AuSCR follow-up team member		X		X	
	Disability/dependence^b^	mRS (baseline: to verify responses from pre-trial is still current, and eligibility is still met for the service) Communication and fatigue (yes/no and 5-point Likert scale, respectively)			X		X	
	Unmet needs	Longer-Term Unmet Needs for Stroke questionnaire [22]			X		X	
	Unplanned hospital readmissions, ED visits^b^	Survey tailored for A-LISTS trial			X		X	
	Serious adverse events^b^	Serious adverse events form specific for A-LISTS trial				X	X	
	Health service use diary for participants	Developed for trial to support recall; used as memory aid at the outcome assessment to respond to questions about current health services used	All participants			X		
Process evaluation	Satisfaction & experiences with service and study participation	Theory-informed survey and/or semi-structured interview/focus groups	Intervention participants				X	
	Satisfaction with service, including implementation features & intervention fidelity	Theory-informed survey and semi-structured focus groups [23, 24]	Service coordinator and clinicians					X
	Participation numbers, recommended actions, uptake of service coordinator recommendations	Template tailored for A-LISTS study; patient-level data will be aggregated	Service coordinator			X		
	Project documentation	Standard operating procedures, minutes, training documents, project notes	Project team, investigators	X	X	X	X	X
Economic evaluation	Current health services used, medications, costs^b^ Programme delivery costs	Resource use questionnaire developed for trial Research (financial) documents, invoices			X		X	

*Abbreviations*: *AuSCR* Australian Stroke Clinical Registry, *EQ-5D-3L* EuroQol 5-dimension 3-level survey; *mRS*, modified Rankin Scale

^a^Standard Australian Stroke Clinical Registry follow-up survey completed 90-180 days after admission

^b^indicates data will also be used for the economic evaluation

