#### Control group

Participants in the control group will receive their usual care (e.g. existing services or supports) in the community. They will also be provided with an electronic/paper diary to record health and community care contacts and referrals used to complete the outcome assessment conducted 12–14-weeks post-randomisation. At the end of the trial, information about participants in the control group who will be assessed as having ongoing high levels of unmet needs will be passed to the hospital team, who may choose to offer follow-up within current services available to them.

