#### Safety monitoring

Occurrence of serious adverse events (SAEs) will be documented throughout the feasibility RCT by the service coordinator and blinded outcome assessor. Relevant information will be obtained from the participant and/or proxy and hospital medical records (where possible by the service coordinator accessing the medical records). SAEs are defined as any untoward or serious medical occurrence that results in death, life-threatening incidents, hospitalisations, an event that results in new disability/incapacity, or other important medical events [34]. SAEs will be reported to a neurologist who will act as the medical monitor (author [name]) for adjudication. If the SAE is deemed to be related to the study intervention, then a report will be submitted to the ethics committee and the local research governance office.

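### Self-reported resource use is topped up from service records in the intervention arm only, so the comparison of service use and cost with usual care rests on unequal ascertainment

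*Protocol article*

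**What the plan says.** The Research aims include "cost implications of the tailored hospital-led follow-up service for chronic stroke compared with usual care (control"), and resource utilisation belongs to the same comparison. Table 1 labels the use of health and community services, and the cost or cost offsets arising from it, as self-reported.

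The source common to both arms is described under Economic evaluation: "Data from participants will be self-reported, with a diary provided for the duration of the study". The Control group section gives controls the same aid: "They will also be provided with an electronic/paper diary to record health and community care contacts". Table 2 describes the diary as a memory aid for the outcome assessment.

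The Economic evaluation section continues: "This information will be supplemented by data from the follow-up service records of all referrals and service contacts for intervention participants". It names no matching source for controls. It adds that medical records may be audited, without saying in which arm or by what rule.

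On safety, the Safety monitoring section says: "Occurrence of serious adverse events (SAEs) will be documented throughout the feasibility RCT by the service coordinator and blinded outcome assessor". The sources are the participant or proxy and "hospital medical records (where possible by the service coordinator accessing the medical records"). The section on randomisation and blinding says: "Service coordinators delivering the intervention will be unaware of participants from their hospital randomised to the control group". In Table 2, serious adverse events carry the footnote that "indicates data will also be used for the economic evaluation".

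**The concern.** The same quantity, service use by participants, is measured from one source in the control arm and from two in the intervention arm. If self-report misses anything and the records recover some of it, the intervention arm shows more use and more cost even when true use is equal.

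The direction makes this awkward. The service works by arranging referrals, so more referrals and contacts is its expected true effect. A surplus created by fuller recording cannot afterwards be separated from that effect, and it could hide a cost offset. The economic results are meant to refine the service and a later effectiveness trial. A larger trial that kept the same method would carry the same bias with less sampling noise around it.

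A weaker version of the problem affects serious adverse events, because the coordinator works with one arm only.

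**Working it through.** The protocol states no figure on this point, so there is nothing to reproduce. The check sets the passages side by side and then bounds the effect under stated assumptions.

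**Resource use: sources by arm**

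| Source | Intervention | Control |
|---|---|---|
| 12–14 week questionnaire with diary | yes | yes |
| Follow-up service records of referrals and contacts | yes | none |
| Medical-record audit | optional, arm not stated | optional, arm not stated |

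Could the service records be meant only for costing delivery? The section costs delivery separately, from interviews with clinical leads and from finance departments. The sentence about service records follows the description of participants' own data and supplements that. As written, the records enter the resource-use data.

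**Bound on the effect**

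Let *s* be the share of contacts captured by self-report with diary, equal in both arms, and *c* the share of missed contacts that the service records recover. With equal true use:

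- control records *s* of the true contacts
- intervention records *s* + (1 − *s*)*c*
- spurious ratio = [*s* + (1 − *s*)*c*] / *s*

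Both *s* and *c* are assumptions; the documents give neither.

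| *s* | *c* = 0.25 | *c* = 0.5 | *c* = 1 (ceiling, 1/*s*) |
|---|---|---|---|
| 0.9 | 0.925/0.9 = 1.03 | 0.95/0.9 = 1.06 | 1/0.9 = 1.11 |
| 0.8 | 0.85/0.8 = 1.06 | 0.90/0.8 = 1.13 | 1/0.8 = 1.25 |
| 0.7 | 0.775/0.7 = 1.11 | 0.85/0.7 = 1.21 | 1/0.7 = 1.43 |

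The last column is a ceiling: it supposes that the records recover every missed contact of every kind, although they cover only referrals and service contacts. The ratio is 1 if self-report misses nothing (*s* = 1) or the records add nothing (*c* = 0). It is also 1 if both arms are compared on the common source alone.

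**Serious adverse events**

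Coordinators document events and are the stated route, where possible, to hospital records. They do not know who the controls are, so neither coordinator route can work for controls. Control capture remains through the blinded assessor: Table 2 marks these events both during the 12 weeks and at 12–14 weeks, in the block completed by all participants. It is thinner, not absent.

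For scale only, assume a true risk of 20% in both arms of 50, *s* = 0.8 and *c* = 0.5. Recorded events are 50 × 0.2 × 0.8 = 8 in control and 50 × 0.2 × 0.9 = 9 in intervention, a spurious difference of 2 points. The 95% half-width for the difference is 1.96 × √(2 × 0.2 × 0.8 / 50) = 15.7 points. These capture values are illustrative and have no basis in the documents.

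**The case against.** The strongest reply is that Table 1 already defines these outcomes as self-reported, so the comparison would rest on the common source anyway. On that reading the service records only add contacts made by the service itself, which are a proper intervention cost with no control counterpart. An article may also leave the reconciliation rule to a fuller document. Part of this stands: the coordinator's own contacts do belong to one arm. But the text commits to supplementing the participants' data, extends this to all referrals, and costs delivery elsewhere. That is a stated rule at odds with Table 1, not an omitted detail.

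It is also fair that the economic analysis is a descriptive cost-consequences presentation, that the statistical section acknowledges the limits of between-group comparison in a feasibility trial, and that no progression criterion uses between-arm costs. This lowers the severity without removing the inconsistency.

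A reader might infer more than the documents support:

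- *That emergency visits and admissions are inflated too.* Table 1 defines them as self-reported, Table 2 collects them by survey with a blinded team member, and nothing says that the service records hold them.
- *That control adverse events surface only if recalled at one final call.* Table 2 marks capture during the 12 weeks as well, and the Safety monitoring section does not restrict participant, proxy or hospital-record sources to one arm.
- *That a safety comparison is biased.* No between-arm test of serious adverse events is planned. The progression criterion concerns events related to the intervention or study procedures and is not comparative; fuller intervention-arm capture makes it more cautious.

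**Conclusion.** The point holds for resource use and cost. The protocol supplements a self-reported outcome from a second source in the intervention arm only and compares the result with usual care. The expected direction is higher apparent use and cost in the intervention arm.

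The size cannot be derived from the documents. With self-report capture assumed at 70% to 90% and equal in both arms, the spurious ratio is at most 1.43 to 1.11, and less with partial recovery. These ceilings should not be carried over to hospitalisations, deaths or other serious adverse events, for which the documents support no capture rate. For those events the finding is limited to thinner capture among controls, which matters if counts are shown by arm or feed the costs.

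Severity is minor to moderate. Completion, attendance and satisfaction, the primary outcomes, are untouched.

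**What to change.** In the Economic evaluation section, state that:

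- between-arm comparisons of resource use and costs use only the 12–14 week questionnaire with diary, which both arms complete;
- follow-up service records are used only for the cost of delivering the intervention, for fidelity and for uptake of referrals (Table 2 already lists coordinator-recorded actions and uptake under process evaluation);
- any medical-record audit follows the same rule in both arms.

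Where serious adverse event counts are shown by arm or enter the costs, label them by source and show those known only through the coordinator separately. Reporting to the medical monitor stays as it is.

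The cost is analysis wording and slightly less complete intervention-arm data in the comparative tables; the fuller data can still be reported descriptively. Recruitment was unfinished at submission (Trial status: 50 randomised by 1 May 2024), so, on that status, the wording could be settled before analysis.

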#### Statistical and data analyses

An independent statistician will conduct the analysis blinded to group allocation. Intention-to-treat and per protocol analyses (*participants who did not 'drop out' of service/withdraw or failed to attend service coordinator appointments*) will be described. Descriptive statistics will be reported for the participants’ characteristics, retention and completion of outcome measures by group allocation (intervention or control). The difference between groups for the primary outcome (completion of the feasibility trial) will be described as a difference in proportions. Other feasibility outcomes, including the proportion of intervention participants that attended the follow-up service, will be reported descriptively.

We acknowledge the limitations of between- and within-group comparisons of effectiveness in feasibility trials and the imprecision that small samples can create [39]. We will also assess within group changes to assess for minimum clinically important effects.

The EQ-5D-3L domains at pre-trial/baseline determined entry into the trial as people experiencing extreme health problems. We will describe the change in the proportion of participants with extreme health problems at 12 weeks between groups using the original criteria for entry into the trial. The EQ-5D-3L dimension responses will also be converted into a utility score using previously published algorithm for Australia [21]. Due to the anticipated skewed distribution of continuous health outcomes measures (e.g., utility values), between-group differences will be reported as median difference. Imputation of missing data will be undertaken as necessary. Multivariable median, logistic, and ordinal logistic regression models adjusted for baseline values to assess differences in health outcomes (e.g. VAS, EQ-5D-3L, LUNS, mRS) between groups. Confidence intervals will be reported for secondary health outcomes to inform discussion of the likely treatment effects of the intervention [40].

Open interview/focus-group transcripts, open-ended responses from the satisfaction surveys, and project documentation/field notes will be analysed using thematic and/or content analysis techniques. Both inductive and deductive methods may be incorporated as appropriate, within a framework analysis approach [41]. Ongoing discussions with the research team will be used to ensure the data are being interpreted and summarised to best reflect the intended meaning. Closed questions will be summarised descriptively. Use of triangulation, involving the combination of multiple data sources, methodological approaches and analysis methods [42], will be used to ensure comprehensiveness and encourage a more reflective analysis of the trial.

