#### Sample size

Up to 100 people with stroke will be recruited (50 for intervention and 50 for control), which is consistent with recommendations for pilot and feasibility studies [29, 30]. It is anticipated that each participating hospital will provide the intervention to approximately 10–15 people, with a capacity of providing the follow-up service to 1–2 intervention participants per week.

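### The health-outcome models adjust for baseline values but name neither age group nor sex, the two factors on which randomisation is stratified

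*Protocol article*

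**What the plan says.** In the protocol article, the section on randomisation, allocation concealment and blinding has participants allocated 1:1, with "Online randomisation will occur using REDCap [17], stratified by age" (under 65 against 65 and over) and sex. The reason given is "to ensure balance of age and sex between the two groups as these factors are associated with differences in HRQoL".

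Statistical and data analyses describes the between-group health-outcome models as "Multivariable median, logistic, and ordinal logistic regression models adjusted for baseline values to assess differences in health outcomes", with VAS, EQ-5D-3L, LUNS and mRS as examples. No other covariate is named. Confidence intervals for these secondary outcomes are meant to inform discussion of likely treatment effects.

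One secondary outcome in Table 1 is a composite: an extreme problem on the EQ-5D-3L, or a VAS of 60 or less. The same definition appears in the inclusion criteria. Table 2 has the baseline EQ-5D-3L collected "to verify responses from pre-trial is still current, and eligibility is still met for the service". The analysis section says that the change in the proportion with extreme problems will be described between groups, "using the original criteria for entry into the trial".

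Under Sample size: "Up to 100 people with stroke will be recruited (50 for intervention and 50 for control"). This rests on feasibility guidance, with no power calculation.

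**The concern.** The plan calls two factors prognostic and constrains the allocation on them, then states an adjustment set without them. Stratified allocation removes the between-arm variation due to age and sex. A model that omits them leaves that variation in its residual error, so its standard errors are larger than the design warrants. With at most 100 people, and intervals that carry the discussion of likely effects, precision that costs nothing should not be given up.

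The entry-criteria composite raises a related question. If it were modelled with adjustment for its own baseline value, that value would be identical for everyone, and the model would in effect be unadjusted.

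**Working it through.** The plan has no figure to reproduce: the sample size has no alpha, power, effect or SD behind it, and no strength is given for age or sex.

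**Inputs from the article.** Allocation 1:1; two binary stratifiers, so four strata; 100 randomised; retention above 80% as a progression criterion, so about 80 analysed at the threshold.

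**Assumptions.** Correlation of 0.5 between baseline and outcome; permuted blocks (size 4 in the binary and median checks); in those two checks 60% aged 65 or over and 45% female; for the binary outcome, a control event rate of about 65% and a treatment log odds ratio of 0 or -0.85.

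**1. Continuous outcome, linear approximation.** Baseline explains 0.5² = 0.25 of the variance, leaving 0.75. If age and sex explain a further share r of total variance, their share of the residual is r/0.75. Omitting them multiplies interval width by 1/√(1 − r/0.75).
- r = 0.02: 1/√(1 − 0.027) = 1.01
- r = 0.05: 1/√(1 − 0.067) = 1.035
- r = 0.10: 1/√(1 − 0.133) = 1.07

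Simulation (4,000 trials per setting, about 84 analysed) gave mean widths without and with the factors of 0.753 and 0.729 at r = 0.05 (ratio 1.03), and 0.756 and 0.705 at r = 0.10 (ratio 1.07). Coverage without the factors was about 96% at r = 0.10. At r = 0, including them cost 0.3% in width.

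**2. Median regression, which the plan uses for skewed outcomes.** With age and sex explaining 10% of the residual variance (r = 0.075), the model standard error ratio, adjusted to unadjusted, was 0.928 at N = 100 and 0.925 at N = 80. At zero association the ratios were already 0.977 and 0.973, so 2 to 3% of that fall is a feature of the standard error estimator. The real part is about 0.928/0.977 = 0.95. The true sampling SD fell from 0.213 to 0.201 at N = 100 (6%) and from 0.234 to 0.233 at N = 80 (under 1%).

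**3. Binary outcome.** N = 100, treatment log odds ratio -0.85, 1,500 runs per setting; arrows run from without to with age and sex.

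| OR per stratifier | SE of log OR | Estimate | Power | SE ratio, risk difference |
|---|---|---|---|---|
| 1.0 | 0.416 → 0.422 | -0.883 → -0.903 | 0.593 → 0.590 | 1.00 |
| 1.6 | 0.415 → 0.428 | -0.836 → -0.882 | 0.549 → 0.552 | 0.986 |
| 2.7 | 0.413 → 0.448 | -0.786 → -0.903 | 0.497 → 0.525 | 0.948 |
| 4.5 | 0.411 → 0.476 | -0.709 → -0.912 | 0.425 → 0.479 | 0.897 |

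For the risk difference, omission widens the interval by 1/0.986 = 1.4%, 1/0.948 = 5% and 1/0.897 = 11% at odds ratios of 1.6, 2.7 and 4.5. The last case is a very strong pair of predictors: 1 − 0.897² is about 20% of variance.

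For the odds ratio, adjustment widens the interval, but the estimate moves further from zero, so the test gains. At 2.7 the ratio of estimate to standard error goes from 0.786/0.413 = 1.90 to 0.903/0.448 = 2.02. With no treatment effect, the unadjusted type I error was 0.042, 0.035 and 0.027 at odds ratios of 1.6, 2.7 and 4.5, against 0.05. The simulation error is about √(0.05 × 0.95/1500) = 0.006, so only the stronger settings are clearly conservative. Ordinal models were not simulated; the same property of odds ratios applies to them.

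**4. Composite.** The inclusion criterion and the Table 1 composite share one definition, and eligibility is checked again at baseline. Baseline status is therefore positive for every eligible participant. As a covariate it is collinear with the intercept and drops out.

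**The case against.** The strongest reply is that this is a condensed article, the analysis plan is not shown, and the text nowhere says that baseline values are the only covariates. That is fair as far as it goes: an unseen plan may add age and sex. But the article does state an adjustment set, and that set does not follow the stratification it describes elsewhere, so it is worth correcting where it stands.

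It can also be said that the loss is small and errs on the safe side, that the outcomes are secondary, that no progression criterion uses a between-group interval for a health outcome, and that the authors already acknowledge small-sample imprecision. All of this stands and limits the weight of the point. If the factors explain only 2% of residual variance, a formula that charges fully for two extra parameters, √0.98 × √(77/75) = 1.003 at N = 80, shows no gain. Simulated least-squares standard errors were slightly kinder, at 0.990.

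Three stronger readings are tempting but unsupported:
- **Every interval is wider than it need be.** This fails for logistic and ordinal odds ratios, whose intervals widen with adjustment.
- **The composite will be modelled with a useless covariate.** The article says only that the change in proportion will be described, and the composite is not among the examples listed for regression. Nor does the constant value extend to extreme problems alone, because a person can enter through the VAS.
- **Hospital belongs in the models too.** Randomisation is not stratified by hospital. With up to six hospitals, a composite model with treatment, age, sex, VAS, utility and five hospital terms has 10 terms. If 80 are analysed and 65% have the outcome, the rarer category holds 80 × 0.35 = 28 people, about three per term.

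**Conclusion.** The point holds as a minor matter of precision and consistency. The models as stated do not include the stratification factors that the protocol itself treats as prognostic, so inference is somewhat conservative. Median and risk differences would have intervals about 0 to 7% too wide if age and sex explain up to 10% of outcome variance beyond baseline. At the top of that range, the gain is worth about (0.756/0.705)² = 1.15, or 15% more participants; at the bottom it is nil. Logistic and ordinal models would lose up to about three percentage points of power at an odds ratio of 2.7 per stratifier, and about five or six at 4.5, with no narrowing of odds-ratio intervals to be had. These sizes rest on the assumed strength of age and sex, a baseline correlation of 0.5 and the assumed event rate. The 7% comes from a linear model and only approximates median regression.

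The remark on the composite is conditional: it matters only if that outcome is modelled. No feasibility conclusion changes.

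**What to change.** State in Statistical and data analyses that every between-group health-outcome model includes the baseline value of the outcome, age group (as stratified) and sex. Both factors are already known at randomisation. The cost is one sentence and two degrees of freedom.

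Add that if the entry-criteria composite is modelled and not only described, its baseline status is replaced by baseline VAS or baseline utility, and the effect is reported as a standardised risk difference. The EQ-5D-3L, including the VAS, is already collected at baseline. Do not add hospital.
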